## STATISTICAL PLAN AND CONSIDERATIONS

**Sample Size Determination** To detect a mean difference in  $\Delta$ -creatinine of  $\geq 0.35$  mg/dL at conventional two-sided (type I error)  $\alpha = 0.05$  and power of 80% requires measurements on 65 patients per treatment group (130 total). **This** sample size of 65 patients per group does not provide adequate power around the secondary endpoint to detect a decrease in the development of stage 2 AKI. At this size we have 80% power to detect a 70.9% reduction the development of Stage 2 AKI. At a cutoff of greater than 0.01 over 30% of all patients enrolled are at risk for developing Stage 2 AKI. Thus by enrolling 90 patients per arm we are able to ensure that we achieve 80% power for the primary and have 80% power to detect a 60% reduction in the development of Stage 2 AKI. Should every patient enrolled stay in the study we will have even more power approaching 90% power for the primary endpoint.

**Statistical Considerations:** *Randomization* Patients will be randomized 1:1 to two arms (standard of care (SOC) vs. ENC using an ESTOP-AKI stratified REDCAP-based algorithm. Assignments will be made within strata of ESTOP-AKI risk scores ( $>0.01$  to 0.569 and  $\geq 0.57$  to protect against imbalances in randomization on key factors (age, race, baseline SCr, severity of illness, patient location ). To balance the number assigned per arm, permuted assignment blocks of variable size that are unknown to investigators will be used.

**Analytic Methods - Primary endpoint:** Difference of mean  $\Delta$ -SCr between the ENC and SOC group. Randomized assignment stratified by predicted risk (ESTOP-AKI score) maximizes the potential for equal distribution of potential confounding factors by treatment group. Primary analysis is thus a comparison of means from a 2-factor (treatment and stratification level) ANOVA model. If there is evidence of imbalance in key factors (baseline SCr, age, sex, hospital service type), then a secondary analysis using linear model methods will be conducted to compare adjusted means. For patients who die within 7-days or receive RRT we will analyze the data with  $\Delta$ -SCr set at their maximum SCr prior these events. **Secondary endpoints:** For binary outcomes (i.e., AKI stage, ICU transfer), proportions will be compared between ENC and SOC groups via the binomial test. The primary analysis will be a direct comparison of these proportions. Logistic regression analysis may be conducted to account for covariate imbalances. Time to discharge (LOS) and time to peak SCr distributions will be compared by group using nonparametric statistics for differences in specific

quantiles (e.g. medians) and other summaries (means). These endpoints can also be approached from a survival analysis modeling perspective, with treatment and other covariates investigated in relation to event rates.

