**Schedule of Events**

| Event                         | Screening      | Enrollment
(Day 0) | Daily
(Days 1-7) | Hospital
Discharge | Follow Up
(Month 3, 6,9,
and 12) |
|-------------------------------|----------------|-----------------------|---------------------|-----------------------|----------------------------------------|
| Demographics                  | X              |                       |                     |                       |                                        |
| Inclusion/Exclusion           | X              |                       |                     |                       |                                        |
| ESTOP-AKI Risk
Assessment  | X              |                       |                     |                       |                                        |
| Informed Consent              |                | X                     |                     |                       |                                        |
| Blood Collection c |                | X                     | X                   | X                     |                                        |
| Urine Collection c |                | X                     | X                   | X                     |                                        |
| Early Nephrology
Consult   |                | X a        |                     |                       |                                        |
| Chart Review b     | X b | X b        | X b      | X b        | X b                         |
| Follow Up Phone
Calls      |                |                       |                     |                       | X                                      |

**Primary Endpoint Definition** -The primary endpoint of interest,  $\Delta$ -SCr, is the peak change from study entry in SCr level over a 7-day interval. We define  $\Delta$ -SCr as the maximal change in creatinine over this interval, and aim to detect a clinical difference in  $\Delta$ -SCr between the SOC and ENC treatment groups. On average, in patients with an ESTOP-AKI score  $\geq 0.01$  (the enrollment cutoff), the mean change in SCr in a 7-day interval was 0.369, (standard deviation 0.734).

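### The base sample size of 65 per group does not follow from the protocol's only SD (0.734): 80% power needs 70 to 71 per group, and 65 gives about 77%

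*Protocol*

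**What the plan says.** The Sample Size Determination paragraph (Protocol, Statistical Plan and Considerations) sets a target difference of 0.35 mg/dL in mean Δ-SCr with a "conventional two-sided (type I error") alpha of 0.05, and states that 80% power "requires measurements on 65 patients per treatment group (130 total"). It gives no SD at that point.

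The SD appears under Primary Endpoint Definition (Protocol, Study Design). For patients with an ESTOP-AKI score of at least 0.01, which is the enrolment cutoff, "the mean change in SCr in a 7-day interval was 0.369, (standard deviation 0.734"). No other SD for this endpoint is given.

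The same sample size paragraph ties a detectable 70.9% reduction in Stage 2 AKI to 65 per group. It then raises enrolment to 90 per arm, partly for that secondary endpoint, and adds: "Should every patient enrolled stay in the study we will have even more power approaching 90% power for the primary endpoint". Allocation is equal ("Patients will be randomized 1:1 to two arms"). The primary analysis is a "comparison of means from a 2-factor (treatment and stratification level) ANOVA model". No dropout rate is given.

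**The concern.** The stated difference, alpha, power and allocation, together with the only SD in the document, fix the sample size, and they do not give 65. The SD describes the endpoint and the population being powered, so it is the natural planning value.

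The figure matters because it counts patients with measurements, not patients enrolled. With no dropout rate stated, the gap between 65 and 90 is the only visible loss allowance for the primary endpoint. Someone following retention against 65 per arm would believe that 80% power was preserved when, on the protocol's SD, it had fallen to about 77%.

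**Working it through.** **Inputs.** Difference 0.35 mg/dL, two-sided alpha 0.05, power 80%, 1:1 allocation, and 65 and 90 per arm (all from Statistical Plan and Considerations); SD 0.734 (Primary Endpoint Definition).

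**Step 1: try to reproduce 65.** Normal formula for two means:

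n per group = 2 × [(z₀.₉₇₅ + z₀.₈₀) × SD / difference]² = 2 × [(1.960 + 0.8416) × 0.734 / 0.35]² = 2 × 5.875² = 69.04, so 70 per group.

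By the exact (noncentral) t-test, 70 per group gives 79.99% and 71 gives 80.6%, so 71 is the strict answer. The stated 65 is not reproduced; it is short by 5 to 6 per group.

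**Step 2: power at the relevant sizes, SD 0.734.** The standard error of the difference is SD × √(2/n). At n = 65 it is 0.734 × √(2/65) = 0.1288, and 0.35 / 0.1288 = 2.718. Normal-approximation power is Φ(2.718 − 1.960) = 77.6%.

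| Per group | Power, t-test | Power, normal |
|---|---|---|
| 65 | 77.0% | 77.6% |
| 70 | 80.0% (79.99%) | 80.5% |
| 71 | 80.6% | 81.1% |
| 90 | 88.9% | 89.2% |

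The last row agrees with the protocol's claim for full retention. Using the two-factor ANOVA degrees of freedom (2n − 3) leaves the t-test figures unchanged to one decimal.

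**Step 3: do standard variants give 65?** A one-sided test needs 55. Allowing for Wilcoxon efficiency gives about 70 / 0.955 = 73.3, so 74. Neither gives 65.

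**Step 4: what would make 65 right?** Any one of these would:
- an SD of 0.707 (t) or 0.712 (normal);
- a difference of 0.363 (t) or 0.361 (normal);
- a stratum factor that explains about 6% to 7% of the variance: 1 − (0.712/0.734)² = 5.9%, or 1 − (0.707/0.734)² = 7.2%.

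The protocol states none of them.

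**Step 5: loss that 90 per arm can absorb at 80% primary power.**
- Down to 65: 1 − 65/90 = 27.8%.
- Down to 70: 1 − 70/90 = 22.2%.
- Down to 71: 1 − 71/90 = 21.1%.

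**The case against.** The strongest reply is that 65 is an intermediate figure. The trial enrols 90 per arm, which gives about 89% power on SD 0.734, so the operative claims (180 patients, at least 80% primary power) stand. This is right, and it is why the point is minor.

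Second, the harm depends on loss that may not occur. The protocol never says that 28% loss is tolerable; that figure is only what 65 out of 90 implies. The document also limits missing endpoints. Research samples supply SCr on days without a clinical value, patients stay in data collection after a non-research consult, and patients who die or receive RRT are analysed with their maximum SCr before the event. All of this stands. The shortfall appears only if more than about 21% to 22% of an arm lacks the endpoint, and at exactly 65 it is 2.4 to 3.0 percentage points.

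Third, 0.734 is a marginal SD, whereas the planned ANOVA uses a within-stratum error SD. If the stratum explained 6% to 7% of the variance, 65 would be correct. This is possible but unstated, so the protocol should be allowed either to correct the number or to state the assumption behind it.

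A reader might go further and infer that the paragraph contradicts itself, because an SD that makes 65 correct gives about 91% power at 90 per arm, above the level the text says is being approached. The documents do not support that. With an SD of 0.715, power is 79.1% (t) or 79.7% (normal) at 65 and 90.4% (t) at 90, so one SD can fit both statements to rounding. The phrase about 90% is too loose to separate these values.

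**Conclusion.** The stated requirement of 65 per group (130 total) does not follow from the protocol's own inputs. With SD 0.734 it is 70 per group by the normal formula or 71 by the exact t-test (140 or 142 total), and 65 gives about 77% power instead of 80%. The tolerable loss from 90 per arm is about 21% to 22%, not 28%.

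This rests on one inference: that the planning SD is 0.734. It is the only SD in the document, it belongs to the stated endpoint and population, and it reproduces the power claimed at 90 per arm. It also assumes no variance reduction from the stratum factor, since none is stated.

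The correction is minor. Enrolment of 180 and the full-retention power statement both stand. A reader might infer that the trial is underpowered for its primary endpoint as planned; it is not. The 70.9% Stage 2 AKI figure is tied to the same base size and would move with it. No replacement value is offered here, because the protocol gives neither the method behind it nor an exact control rate, saying only that the rate is above 30%.

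**What to change.** In Sample Size Determination, do one of two things:

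1. Replace 65 per group (130 total) with 71 per group (142 total), or with 70 per group (140 total) while stating that the normal approximation was used, and name the SD of 0.734 in the same sentence; or
2. Keep 65, state the residual SD (about 0.71) or the variance reduction from the stratum factor that yields it, and reconcile that with the SD in the primary endpoint definition.

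Under option 1, add that 90 per arm keeps 80% primary power only down to about 70 to 71 measured patients per arm, a loss of about 21% to 22%. The sponsor should also recompute the detectable Stage 2 AKI reduction at the corrected base size, stating the method and the control rate used.

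The cost is a few words and one recalculation. No patients are added, and neither the analysis nor the conduct of the trial changes.

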### **ESTOP-AKI DEVICE**

The electronic risk prediction algorithm (ESTOP-AKI) being studied will interface with Epic to determine the likelihood for the patient to develop AKI. The study team is creating the algorithm with the help of software engineers and architects from UofC CBIS. ESTOP-AKI will use the following information from Epic:

- Medical Record Number
- Name
- Age
- Sex
- vital signs (respiratory rate, heart rate, temperature, pulse pressure index, systolic and diastolic blood pressure, oxygen saturation, and mental status)
- laboratory values (complete blood count, liver function panel, and blood chemistries/basic metabolic panel).

Upon generation of a risk level, ESTOP-AKI will electronically notify a member of the study team the eligibility status of the patient.

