**Inclusion Criteria**

- a) Age >18 years old
- b) Initial E-STOP AKI score  $\geq 0.01$  within the last 12 hours.

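### The randomisation strata leave out an eligible score of exactly 0.01, and the primary model uses only a two-level version of a risk score that the trial holds in full

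*Protocol*

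**What the plan says.** The Inclusion Criteria require "Initial E-STOP AKI score $\geq 0.01$ within the last 12 hours". The Specific Aim uses the same limit, and so does the Primary Endpoint Definition, which calls it the enrolment cutoff.

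The Randomization paragraph of the Statistical Plan says: "Assignments will be made within strata of ESTOP-AKI risk scores". The lower stratum runs from above 0.01 to 0.569 and the upper stratum starts at 0.57. The stated purpose is "to protect against imbalances in randomization on key factors (age, race, baseline SCr, severity of illness, patient location". The Sample Size paragraph also uses a strict inequality: "At a cutoff of greater than 0.01 over 30% of all patients enrolled are at risk".

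The Analytic Methods paragraph makes the primary analysis a comparison of means from an ANOVA with two factors, treatment and stratum. If baseline creatinine, age, sex or hospital service type looks imbalanced, a secondary adjusted linear model follows.

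The ESTOP-AKI Device section lists what the score uses: record number, name, age, sex, vital signs including mental status, and "laboratory values (complete blood count, liver function panel, and blood chemistries/basic metabolic panel". Race and ward location are not listed. The Background says only that the model draws on demographics along with vital signs and laboratory values.

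**The concern.** Three things do not fit together.

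- **Coverage.** Eligibility includes 0.01 and the lower stratum excludes it. The stratum is both the randomisation factor and a factor in the primary model, so such a patient has no defined place in either.
- **Information.** The primary model carries the risk score only as low or high. The trial generates the full score at screening to decide eligibility, so the rest of its prognostic information is available but unused.
- **The balance claim.** Strata built on one score can balance other factors only as far as those factors track the score. For race and location the protocol gives no reason to expect that.

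At stake are a clean definition for the randomisation system and the analysis, some precision in the primary comparison, and the accuracy of one sentence of rationale.

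**Working it through.** **1. Coverage**

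| Score | Eligible (≥0.01)? | Stratum |
|---|---|---|
| exactly 0.01 | yes | none |
| above 0.01, up to 0.569 | yes | lower |
| above 0.569, below 0.57 | yes | none, unless held to three decimals |
| 0.57 or more | yes | upper |

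Three decimals would close the second gap. The first stays open at any precision, because 0.01 fails a strict inequality.

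**2. Factors said to be protected**

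Of the five factors named, age is a listed input, baseline creatinine is plausibly covered by the blood chemistries, and vital signs and mental status bear on severity of illness. Race and location are not listed. A simulation of stratified permuted blocks (180 patients, block sizes 4 and 6 assumed, 3,000 runs) gave the SD of the between-arm difference in a standardised covariate:

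- Uncorrelated with the score: about 0.148 with or without strata.
- Correlation 0.6, half the patients in the upper stratum: 0.130 with strata, 0.145 without, about a 10% reduction.
- Correlation 0.6, 2% in the upper stratum: 0.147 against 0.148.

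**3. The planned power**

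Inputs from the protocol: difference 0.35 mg/dL, SD 0.734, 90 per arm, two-sided 5%. The standardised difference is 0.35/0.734 = 0.477, and a two-sample t-test then has 88.9% power. This agrees with the protocol's statement that full retention brings power close to 90%, so the sample size takes no credit for stratification.

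**4. What the continuous score adds to the stratum**

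Not in the protocol, so assumed: the correlation r between score and outcome (0.2 to 0.5), a normal latent score, and the share q of patients at 0.57 or more (1% to 50%).

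- Share of score variance kept by a two-level split: k = φ(z)²/[q(1−q)], where z is the upper-q normal quantile and φ the normal density.
- Residual SD with the stratum only: 0.734·√(1 − r²k).
- Residual SD with the continuous score: 0.734·√(1 − r²), which is 0.719 at r = 0.2 and 0.636 at r = 0.5.

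Worked case, q = 50%, r = 0.5: k = 0.3989²/0.25 = 0.637. The stratum-only SD is 0.734·√(1 − 0.25 × 0.637) = 0.673, giving 93.4% power. The continuous score gives SD 0.636 and 95.7%.

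Power at 90 per arm:

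| q (patients of 180) | k | r = 0.2: stratum → score | gain | r = 0.5: stratum → score | gain |
|---|---|---|---|---|---|
| 1% (about 2) | 7% | 89.0% → 90.1% | 1.1 | 89.4% → 95.7% | 6.2 |
| 5% (9) | 22% | 89.2% → 90.1% | 0.9 | 90.6% → 95.7% | 5.1 |
| 20% (36) | 49% | 89.5% → 90.1% | 0.6 | 92.5% → 95.7% | 3.2 |
| 50% (90) | 64% | 89.7% → 90.1% | 0.4 | 93.4% → 95.7% | 2.2 |

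Gains are percentage points taken before rounding.

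**The case against.** The strongest reply is that little here is an error. Randomisation 1:1 is unbiased whether or not the strata are useful, the planned power does not rely on them, and the protocol has a secondary adjusted analysis in case of imbalance. It says only that stratifying by risk gives the best chance of even distribution, which is not a promise. A two-factor ANOVA is a legitimate pre-specified choice. The gap between 0.569 and 0.57 is probably just three-decimal notation.

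Most of that stands, and it keeps the point small. It does not remove the gap at 0.01. Nor does the fallback supply what is missing: its list contains neither the score nor race nor severity of illness, and it applies only after imbalance is seen.

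Two stronger readings are tempting, and the protocol supports neither.

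- A reader might infer that the strata protect none of the named factors. Age, blood chemistries and vital signs feed the score, so some indirect balance on age, baseline creatinine and severity is possible, though modest.
- A reader might infer from a cut 57 times the entry limit that the upper stratum will be almost empty and that stratification does little. The protocol gives no score distribution. Under an assumed truncated-Pareto score with 1% to 50% in the upper stratum, the stratum explains about 50% to 74% of raw-score variance, but about 12% to 51% on the log scale. The conclusion turns on shape and scale, both unknown. An unexplained cut is not thereby a wrong one.

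**Conclusion.** This is a free improvement, with a small boundary error attached. The error is certain: a score of exactly 0.01 is eligible and has no stratum. The claim of protection for race and location has no support in the listed score inputs. Neither affects validity.

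The power gain from the continuous score is conditional. It is about 0.4 to 6 points at 90 per arm, measured against the stratum-adjusted model that the protocol already specifies. Comparing with a model that has no covariate (88.9%) would overstate it. The upper end needs both a correlation of 0.5 and an upper stratum of 1% to 2%. At a correlation of 0.2 the gain is about one point or less. The figures rest on an assumed correlation, a normal latent score and an assumed upper-stratum share. Whether 0.57 leaves that stratum small cannot be judged from the document.

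**What to change.** 1. Define the strata as ≥0.01 to <0.57 and ≥0.57. Use ≥0.01 wherever the entry limit appears, including the Sample Size paragraph.
2. Keep the stratum in the primary model and pre-specify the continuous ESTOP-AKI score, on the log scale, as a covariate.
3. Limit the balance claim to predicted risk. Drop race and patient location from it.

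The cost is a line of protocol text, a check of the REDCap stratum limits and one covariate already generated at screening. No extra patients or data are needed. If enrolment has begun, keep the allocations already made, record how any score of exactly 0.01 was handled, and add the covariate before outcomes are examined by arm.

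### Study-entry creatinine is kept out of the primary model and adjusted for only if imbalance is seen; fixing it as a covariate would be a near-free gain in precision

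*Protocol*

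**What the plan says.** Under Statistical Plan and Considerations, the Analytic Methods paragraph fixes the primary model: "Primary analysis is thus a comparison of means from a 2-factor (treatment and stratification level) ANOVA model". It then makes covariate adjustment conditional: "If there is evidence of imbalance in key factors (baseline SCr, age, sex, hospital service type), then a secondary analysis using linear model methods" are to be used to compare adjusted means. Baseline SCr is therefore outside the primary model, and enters a secondary one only when imbalance is judged to be present.

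The Primary Endpoint Definition makes Δ-SCr the peak change from the study-entry creatinine over seven days. The study-entry value is thus needed for each patient's outcome.

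The randomization paragraph also treats baseline SCr as important. It gives the purpose of stratifying by score as "to protect against imbalances in randomization on key factors (age, race, baseline SCr, severity of illness, patient location". The strata themselves are formed on the ESTOP-AKI score alone, in two levels.

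**The concern.** A change score is often correlated with the value it is measured from. If that holds here, part of the variance of Δ-SCr could be removed with a number the trial already has for every patient. The planned primary test leaves that variance in.

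The imbalance trigger is a poor way to recover it. Adjustment gains precision because the covariate predicts the outcome, and it does so whether or not the arms differ on it. A rule that adjusts only after visible imbalance skips most of the trials in which adjustment would have helped. It also makes the existence of an adjusted estimate depend on the data. At stake are power and the width of the confidence interval for the primary contrast, and a clean statement in advance of which adjusted result will be reported.

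**Working it through.** **Inputs.** From Sample Size Determination: difference 0.35 mg/dL, two-sided α 0.05, and "power of 80% requires measurements on 65 patients per treatment group (130 total". From Primary Endpoint Definition: "the mean change in SCr in a 7-day interval was 0.369, (standard deviation 0.734". From Number of Subjects: 90 per arm, 1:1. Not in the protocol: r, the correlation of study-entry SCr with Δ-SCr within stratum. It is assumed, over 0 to 0.5.

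**The plan's own figures.** Standard error of the difference = 0.734 × √(2/n).

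- n for 80% power = 2 × (1.960 + 0.842)² × 0.734² / 0.35² = 69.04, so 70 per arm. The stated 65 does not reproduce.
- At 65 per arm: SE = 0.1288; 0.35/0.1288 = 2.718; power = Φ(2.718 − 1.960) = 77.6% (t-based 77.0%).
- At 90 per arm: SE = 0.1094; 0.35/0.1094 = 3.199; power = Φ(3.199 − 1.960) = 89.2% (t-based 88.9%). This agrees with the protocol's statement that power approaches 90%.

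The shortfall at 65 is a separate matter and does not affect this point.

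**Effect of adding study-entry SCr.** Residual SD = 0.734 × √(1 − r²). Power is t-based for 0.35 mg/dL:

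| r (assumed) | Residual SD | Power, 65 per arm | Power, 90 per arm |
|---|---|---|---|
| 0 | 0.734 | 77.0% | 88.9% |
| 0.2 | 0.719 | 78.6% | 90.1% |
| 0.3 | 0.700 | 80.7% | 91.5% |
| 0.5 | 0.636 | 87.6% | 95.7% |

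**Cost if the covariate is useless (r = 0).** One error degree of freedom is lost, and the variance rises by a factor of about 1 + 1/(2n − 5) because of chance imbalance in the covariate. Power goes from 88.9% to 88.7% at 90 per arm, and from 77.0% to 76.6% at 65 per arm.

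**What a trigger recovers.** As the protocol is written, the primary test gains nothing, because the adjusted model stays secondary. A more generous reading lets the adjusted result replace the ANOVA whenever imbalance is seen. This was simulated with 20,000 trials per setting, 90 per arm, and an assumed trigger of p < 0.10 on study-entry SCr:

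| r | ANOVA | Always adjusted | Adjusted only if triggered |
|---|---|---|---|
| 0.3 | 88.5% | 91.0% | 89.1% |
| 0.5 | 88.7% | 95.6% | 90.3% |

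At r = 0.5 the trigger recovers 1.6 of 6.9 points, and at r = 0.3 it recovers 0.6 of 2.5.

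**Type I error.** Across the settings simulated (r of 0, 0.3 and 0.5; 65 and 90 per arm), it was 4.7% to 5.1% for the ANOVA and 4.8% to 5.2% for the always-adjusted model. Taking the better p-value only when the trigger fired gave 4.8% to 5.3%.

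**The case against.** The primary analysis involves no data-driven choice. It is fixed without conditions, the trigger governs only a model labelled secondary, and the two results are already ranked. Power at the planned 90 per arm is about 89%, and the benefit of adjustment rests on a correlation that the protocol does not report. All of this stands, and it limits the point to precision and prespecification.

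Several stronger readings are tempting, and the protocol does not support them.

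- **Bias.** A reader might infer that chance imbalance in entry creatinine biases the ANOVA. Over stratified randomization the contrast is unbiased. Such imbalance is sampling variation that the standard error already covers.
- **Inflated α.** In simulation, free choice between the two analyses in every trial gave about 6.5% to 7.5% at r of 0.3 to 0.5. The protocol does not allow that choice.
- **Strata too wide.** The lower stratum runs from 0.01 to 0.569, about 57-fold. A ratio of score limits says nothing about the spread of creatinine within the stratum, and the protocol says that stratification protects against imbalance, not that it guarantees balance.
- **Contradictory factor lists.** The randomization list and the adjustment list differ, but one explains stratification and the other names candidates for adjustment. Both include age and baseline SCr.
- **Little power to spare.** The 77% figure applies only if 25 of 90 patients per arm (28%) are lost, a rate the protocol does not state.

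The missing imbalance criterion is also no fault here, since a statistical analysis plan could supply it. The conditional structure and the omission from the primary model, however, are set by the protocol itself.

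Blood chemistries feed the ESTOP-AKI score, so the stratum may already absorb some of what study-entry SCr predicts. That is why r must be read as the correlation left within stratum, and why the range has to start at zero.

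**Conclusion.** The point holds as an improvement in precision to a valid, prespecified analysis. At 90 per arm the gain runs from nothing at r = 0, through about 1 point at r = 0.2 and 2 to 3 points at r = 0.3, to about 7 points at r = 0.5. At 65 per arm the corresponding gains are about 0, 2, 4 and 11 points. The downside is at most about 0.2 points at 90 per arm and 0.3 at 65. These figures rest on the protocol's SD of 0.734 applying within stratum, on a linear relation between study-entry SCr and Δ-SCr, and on assumed values of r.

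Confidence is high about what the protocol fixes and about the low cost of changing it. The size of the benefit is uncertain because it depends on r. An imbalance trigger would forfeit roughly three quarters of whatever gain exists, under the simulated trigger.

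**What to change.** - Make the primary analysis an ANCOVA of Δ-SCr on treatment, ESTOP-AKI stratum and study-entry SCr, whatever the observed balance. Name the covariate as the value used to compute Δ-SCr, because the protocol's term baseline SCr is not defined.
- Keep the two-factor ANOVA as a supportive analysis.
- Run the secondary model adjusted for age, sex and hospital service type in all cases, and remove the imbalance condition. Fixing study-entry SCr alone would leave those three covariates data-dependent.
- The continuous ESTOP-AKI score is an optional further covariate. Its added value was not examined here.

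The cost is a change of wording and one degree of freedom in the primary model. No extra patients or measurements are needed. The change should be made before outcome data are examined by arm, including at the planned futility and efficacy look at half enrollment.

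### For patients who die or receive RRT, the protocol sets the change variable Δ-SCr to an absolute creatinine level, so the primary endpoint as written mixes two scales

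*Protocol*

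**What the plan says.** Three statements in the protocol bear on this point.

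- **Definition** (Study Design, Primary Endpoint Definition, below the Schedule of Events): Δ-SCr "is the peak change from study entry in SCr level over a 7-day interval". The planning values in the same paragraph are on that scale: "the mean change in SCr in a 7-day interval was 0.369, (standard deviation 0.734").
- **Rule for death and RRT** (Statistical Plan and Considerations, Analytic Methods): "For patients who die within 7-days or receive RRT we will analyze the data with" Δ-"SCr set at their maximum SCr prior these events".
- **Analysis** (same paragraph): "Primary analysis is thus a comparison of means from a 2-factor (treatment and stratification level) ANOVA model".

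The sample size paragraph sets a detectable difference of 0.35 mg/dL in mean Δ-SCr (two-sided 5% level, 80% power) and states that with 90 per arm and no losses the power approaches 90%.

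**The concern.** A maximum creatinine is a level and Δ-SCr is a change. The two differ by the patient's study-entry creatinine. Under the rule as worded, a patient who goes from 1.5 to 2.0 mg/dL and then starts RRT is entered as 2.0, whereas the definition gives 0.5.

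Three consequences follow for the ANOVA if the sentence is programmed as written.

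- Means are taken over a mixture of levels and changes.
- The between-patient variance is larger than the planning SD of 0.734 allows for.
- An arm difference in the frequency of death or RRT moves the estimated treatment effect by an amount that depends on entry creatinine, not on how much kidney function was lost.

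Two analysts working from the same protocol could also build different primary datasets. That should not be settled once outcomes are known.

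**Working it through.** **1. The texts side by side.** The definition subtracts the study-entry value. The death/RRT rule names the maximum SCr and subtracts nothing. No other section qualifies the rule. The conflict is therefore in the wording and needs no arithmetic.

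**2. What the literal rule does to single patients (illustrative values).**

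| Entry SCr | Maximum before event | Event | Literal score | Change score |
|---|---|---|---|---|
| 1.5 | 2.0 | RRT | 2.0 | 0.5 |
| 1.5 | 1.6 | death | 1.6 | 0.1 |
| 3.5 | 3.5 | death | 3.5 | 0 |
| 0.8 | 2.4 | RRT | 2.4 | 1.6 |

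In the second row the literal score is (1.6 − 0.369)/0.734 = 1.68 SD above the planning mean, and the change score is (0.1 − 0.369)/0.734 = 0.37 SD below it. In the last two rows the literal rule gives the higher value to the patient without any rise. Entry creatinine of this size is possible, because the exclusion applies only above 4.0 mg/dL.

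**3. The protocol's own power figures.** Inputs: difference 0.35, SD 0.734, two-sided 5% level, 90 per arm.

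- Power = Φ[0.35 / (0.734 × √(2/90)) − 1.96] = Φ[3.199 − 1.96] = Φ(1.239) = 89.2% (t-test 88.9%). This agrees with the protocol's statement for full enrolment.
- The same inputs at 80% power give n = 2 × (1.96 + 0.842)² × 0.734² / 0.35² ≈ 69.04, rounded up to 70 per group, where the protocol "requires measurements on 65 patients per treatment group (130 total"). That is a separate matter. It does not affect this point, and 90 per arm covers 70.

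**4. Variance under the literal rule.** Let a share e of patients in each arm fall under the rule, independently of their entry SCr and Δ-SCr. Let entry SCr have mean μ and standard deviation s. The analysed value is Δ-SCr plus entry SCr for those patients, so

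SD² = 0.734² + e(μ² + s²) − (eμ)².

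Assumed, not in the protocol: μ = 1.216 and s = 0.57 mg/dL. Then μ² + s² = 1.804.

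| e | SD² | SD | Power for 0.35 at 90 per arm (t-test) |
|---|---|---|---|
| 0 | 0.539 | 0.734 | 88.9% |
| 2% | 0.574 | 0.758 | 86.9% |
| 5% | 0.625 | 0.791 | 84.0% |
| 10% | 0.704 | 0.839 | 79.5% |

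A simulation with log-normal entry SCr gave SDs of 0.757, 0.792 and 0.838 and power of 86.9%, 83.9% and 79.6% for the same three shares. With entry SCr fixed at 1.5 mg/dL, SD = √(0.734² + e(1 − e) × 1.5²) gives 0.763, 0.804 and 0.861, and normal-approximation power of 86.8%, 83.2% and 77.8%.

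**5. Shift from an arm difference in events.** Shift = difference in event share × mean entry SCr = 0.05 × 1.216 = 0.061 mg/dL, which is 0.061/0.35 = 17% of the target difference. For mean entry SCr from 0.8 to 2.0 mg/dL it is 0.04 to 0.10 mg/dL. The shift counts against the arm with more events.

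**6. What remains on the change scale.** A patient who dies before creatinine rises scores near 0, which is 0.369/0.734 = 0.50 SD below the planning mean. Compared with scoring such patients at that mean, a 5-point arm difference in these deaths moves the mean difference by 0.05 × 0.369 = 0.018 mg/dL, about 5% of 0.35.

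**The case against.** The best reply is that the sentence is loose drafting. The quantity being set is still called Δ-SCr, the protocol defines it as a change, and the planning mean, SD and detectable difference are all on that scale. Nothing suggests that a mixed-scale endpoint was intended, and the authors probably meant the change up to the maximum SCr before the event. That is plausible, and it is why one clause repairs the problem. It does not remove the problem, because the sentence as it stands says something else.

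It can also be said that the literal rule acts as a crude penalty, since death and RRT score worse. The protocol does not call it a penalty, and the amount added is the patient's entry creatinine, not the severity of the event.

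The objection to the numbers stands. The protocol gives no 7-day death or RRT rate and no mean entry creatinine. It enrols patients before AKI and excludes those with earlier AKI in the same stay, so affected patients may be few. At 2% the loss is about 2 points of power.

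A reader might go further and infer that the plan scores early death as the best possible result, or that the worst outcomes in general count as favourable. The documents do not support that. It arises only on the change reading, so it cannot be added to the scale error, which belongs to the literal one. Even there, a score near 0 is about half an SD below the mean, and a patient who dies or starts RRT after a rise keeps that rise. Stopping at the start of RRT is reasonable, because dialysis itself clears creatinine.

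**Conclusion.** The conflict is real and lies in the derivation of the primary endpoint: the definition is a change, and the rule for death and RRT assigns a level. Programmed as written, the rule overstates the value of each affected patient by that patient's entry creatinine, inflates the variance, and ties the treatment estimate to arm differences in death or RRT.

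The size cannot be fixed from the protocol. If 2% to 10% of patients are affected and mean entry SCr is about 1.2 mg/dL, power at 90 per arm goes from about 89% to between 87% and 80%, and a 5-point arm difference in events adds about 0.06 mg/dL. Both inputs are assumptions; higher entry values give larger effects and rarer events smaller ones. At the upper end of that range power is still about the 80% that the protocol sets for the primary endpoint, so the main reason to act is that the stated rule is wrong, not that the trial would be underpowered.

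The low score of a patient who dies before any rise is a lesser and conditional matter. It justifies an optional sensitivity analysis and is not an error in the text.

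**What to change.** In Analytic Methods, replace the rule for death and RRT with: *Δ-SCr = (maximum SCr before death or RRT) minus study-entry SCr*. All patients are then on one scale, and the planning SD of 0.734 and the power of about 89% at 90 per arm apply again. The cost is one sentence of wording, with no new data and no extra patients.

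Optional: prespecify one sensitivity analysis of the primary endpoint in which death within 7 days ranks worst and RRT next worst, both above any observed Δ-SCr, tested with a rank test stratified by ESTOP-AKI stratum (van Elteren). The cost is one extra analysis.
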